The Principle Investigator will review all test results and AE report 24h prior to escalation to the next dose level. The dose will be increased based on review of drug toxicity by the Principle Investigator and the Medical Director of Protalix Ltd. A follow up safety visit will take place at Day 29.

Plasma levels of human prGCD will provide a pharmacokinetic profile, including AUC0-inf, Tmax, Cmax and Cmin and will be calculated for each subject.

All PK samples of human prGCD will be analyzed at the end of the study for all subjects. This data will be used as adjunct information for a safety review, which will include a review of adverse events, changes in vital signs, physical examination and clinical laboratory test results. Unexpectedly high plasma concentrations will be reviewed for correlation to related adverse events.

This study is conducted according to FDA and European GCP guidelines.

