## Stopping Criteria

If any subject experiences a serious adverse event, that in the judgment of the Principle Investigators and/or the Medical Director of Protalix Ltd. is life-threatening and definitely related to study medication (see Section 7.2), the study will be stopped

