## Definitions of Severity and Relationship to Study Medication

### Relationship to Study Medication

The following definitions should be used to assess the relationship between an adverse event and the study drug.

Unrelated: The event is clearly related to other factors, such as a subject's clinical state, therapeutic interventions or concomitant medications.

Remotely Related: The event was most likely produced by other factors, such as a subject's clinical state, therapeutic interventions or concomitant medications, and does not follow a known response pattern to the study drug.

Possibly Related: The event has a reasonable temporal relationship to the study drug administration and follows a known response pattern to the study drug. However, a potential alternate etiology may be responsible for the event. The effect of drug withdrawal is unclear. Rechallenge information is unclear or lacking.

Probably Related: The event follows a reasonable temporal sequence from the time of drug administration, and follows a known response pattern to the study drug and cannot be reasonably explained by other factors. There is a reasonable response to withdrawal of the drug. Rechallenge information is not available or advisable.

Related: The event follows a temporal sequence from the time of drug administration and follows a known response pattern to the study drug. It either occurs immediately following the study drug administration, improves on stopping the drug, or reappears on repeat exposure.

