## Serious Adverse Event Reporting

A serious adverse event (SAE) is any event that suggests a significant hazard, contraindication, side effect, or precaution. An SAE is defined as any untoward medical occurrence that at any dose:

- - - Results in death
    - Is life-threatening
    - Requires hospitalization or prolongation of existing hospitalization
    - Results in persistent or significant disability or incapacity
    - Is a congenital anomaly, cancer, overdose or birth defect

Life Threatening is defined as an event where a subject is at risk of death at the time of the event. It does not refer to an event that hypothetically might have caused death if it was more severe. Disability is defined as a substantial disruption of a person's ability to conduct normal life functions. An unexpected adverse event is one that has not been previously observed, or one that is of a specificity or severity not consistent with the current investigator brochure.

Any serious adverse event should be reported to the Sponsor's Monitor by telephone or fax within 24 hours of the event. The call should be followed-up with a written report within five days. Full details of the event, any sequels and an assessment of the relationship to the study drug, must be provided in the report. Any serious adverse events must also be reported to the Institutional Review Board (IRB) within 48 hours and a copy of this report must be sent to the Sponsor's Monitor. Cases of death must be reported immediately to the Hospital Director. Protalix will notify the appropriate regulatory authorities as required.

In the event of an SAE, the Medical Director must be contacted immediately by calling the following telephone # within 24 hours of disclosure of the incident:

[contact]; [name]

All SAEs must be reported to the IRB. The investigator will promptly supply all information identified and requested by the sponsor and its contracted monitor regarding the SAE.

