# SUBJECT WITHDRAWAL

Subjects will be discontinued from the study prematurely if:

1. An intercurrent illness occurs which precludes further treatment.
2. A serious adverse event occurs, which in the judgment of the principle investigator, managing physicians, and/or sponsor, is probably related to the study drug and cannot be acceptably managed.
3. The subject requests to be withdrawn from the study.
4. The principal investigator decides that it is in the subject's best interest.
5. The subject is noncompliant with the protocol.
6. The sponsor decides to discontinue the study.
7. Subjects who participates in another investigational drug trial

All subjects prematurely discontinued from the trial, regardless of cause, will have follow up visits according to the study schedule, for safety. The reason(s) for withdrawal will be recorded in the CRF by the investigator and the occurrence reported to the medical monitor.

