## Institutional Review Board (IRB) Approval

The principal investigator will provide the IRB with all appropriate material, including the protocol, informed consent, investigator brochure, and any advertising materials. The study will not be initiated until the IRB provides written approval of the aforementioned documents and until approval documents have been obtained by the principal investigator and copies received by Protalix Ltd. Appropriate reports on the progress of this study by the principal investigator will be made to the IRB and Protalix Ltd. in accordance with the applicable government regulations and in agreement with policy established by the sponsor.

This study must be approved by an IRB or other ethical approval body prior to subject enrollment. The governing IRB must comply with all the requirements set forth in the ICH guidelines. The IRB is responsible for the initial approval and continuing review of the proposed clinical study. The investigator must retain a copy of the approval letter that contains the study number, protocol title and identification of all documents approved. A copy of the letter must be sent to Protalix prior to drug shipment to the investigator.

The investigator agrees to promptly report to the IRB all unanticipated problems involving risks to human subjects or others.

A final report should be submitted to the IRB and Protalix within three months after completion or termination of the study. The investigator must maintain an accurate and complete record of all submissions made to the IRB, including a list of all reports and documents submitted.

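### No finding obliges a hold on escalation, and the only mandatory study-level stop needs an SAE that is both life-threatening and of top-level causality

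*Protocol*

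**What the plan says.** **Escalation.** Under Section 3 (Study Design) the investigator reviews all test results and the AE report 24 hours before each escalation. Then: "The dose will be increased based on review of drug toxicity by the Principle Investigator and the Medical Director". No grade, number of subjects, laboratory limit or causality level is attached to this decision.

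**Stopping.** Section 3.6 applies to an SAE in any subject that, in the judgement of the investigators and/or the sponsor's Medical Director, "is life-threatening and definitely related to study medication (see Section 7.2), the study will be stopped".

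**Causality.** Section 7.1.1 has five levels: *Unrelated*, *Remotely Related*, *Possibly Related*, *Probably Related* and *Related*. The top level reads: "Related: The event follows a temporal sequence from the time of drug administration and follows a known response pattern to the study drug". The known-pattern element already appears at *Possibly Related*: "The event has a reasonable temporal relationship to the study drug administration and follows a known response pattern to the study drug". It is also part of *Probably Related*.

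**Other safeguards.** Section 8 item 2 withdraws a subject for an SAE that "is probably related to the study drug and cannot be acceptably managed". Item 4 lets the investigator withdraw a subject in that subject's best interest. Item 6 reads "The sponsor decides to discontinue the study" and gives no criterion. Section 7.2 sends SAEs to the sponsor within 24 hours and adds: "Any serious adverse events must also be reported to the Institutional Review Board (IRB) within 48 hours". Section 10.2 adds: "The investigator agrees to promptly report to the IRB all unanticipated problems involving risks to human subjects or others". Sections 3 and 6.2 allow a slower infusion after an adverse effect. CTC version 2.0 grading is required (Sections 5.6.3 and 7.1.2) but is tied to no dosing decision.

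**The concern.** The primary objective is the safety of escalating doses. The subjects are healthy volunteers with no expected benefit, and Section 1.1 calls this the first trial of the plant-cell enzyme. All six receive every level, and the dose doubles from 15 to 30 and from 30 to 60 units/kg a week apart.

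With no limit fixed in advance, the same findings could lead to escalation or to a hold. The review also works without exposure or antibody results, because both are analysed at the end of the study (Sections 3 and 5.4). Clinical and routine laboratory findings therefore carry the decision, and no threshold is set for them. The one binding rule covers only the extreme case, and it depends on a causality level that a new kind of reaction may not reach.

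**Working it through.** The protocol states no operating characteristic or event rate, so there is no figure to reproduce. The main check sets the provisions side by side.

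**Step 1: what each finding obliges, as written**

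| Finding at one active dose | Section 3.6 | Section 8 | Section 3 review |
| --- | --- | --- | --- |
| Life-threatening SAE, *Related* | Study stops | Not needed | Not needed |
| Life-threatening SAE, *Probably Related* | Not met | Affected subject leaves if the event cannot be acceptably managed | Takes place; outcome not fixed |
| SAE not life-threatening, any related level | Not met | As above if at least probably related; otherwise discretion | Takes place; outcome not fixed |
| Related grade 3 reactions in several subjects, none serious | Not met | Discretion only | Takes place; outcome not fixed |

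Only the first row obliges action for the whole group. The reporting duties in Sections 7.2 and 10.2 permit a hold but do not require one.

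**Step 2: can a new reaction reach the required level?** *Possibly Related*, *Probably Related* and *Related* all require a known response pattern to the study drug. Section 1.2 reports no obvious treatment-related adverse reactions in the two animal studies (preliminary results for the second), so it supplies no pattern. A novel reaction with close timing and no other explanation fails the known-pattern element of those three levels. It does not fit the two lower levels either, since those attribute the event to other factors.

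**Step 3: what a hold rule would cost (assumed rates).** Let p be the true rate of related grade 3+ events per subject at a dose level, with six independent subjects. For a hold at 2 or more of 6:

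H(p) = 1 − (1−p)^6 − 6p(1−p)^5

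- p = 0.05: 1 − 0.7351 − 0.2321 = 0.0328
- p = 0.10: 1 − 0.5314 − 0.3543 = 0.1143
- p = 0.20, 0.30, 0.50: 0.345, 0.580, 0.891

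For comparison, a hold at 1 or more of 6, 1 − (1−p)^6, gives 26.5% at p = 0.05 and 46.9% at p = 0.10.

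Over the two active escalation steps, independence between levels gives 1 − (1−H)^2, which is 6.4% at p = 0.05 and 21.5% at p = 0.10. The same people are re-exposed, so independence is doubtful. Whatever the dependence, the two-step figure lies between H and 2H: 3.3% to 6.6%, and 11.4% to 22.9%.

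For a hold on any related SAE at rate s per subject per dose, 1 − (1−s)^6 gives 0.6%, 3.0% and 5.9% per level at s = 0.1%, 0.5% and 1%.

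**The case against.** The strongest reply is that escalation is already controlled. Section 3 requires a review by two parties before each step, the sponsor can end the study at any time, and the investigator can withdraw any or all of the six. Because the same six subjects receive every level, withdrawing an affected subject keeps that person from the doubled dose. Prior use of 30 and 60 units/kg with other preparations (Section 3.5) lowers the expected risk. All of this stands. It narrows the gap to subjects not yet affected, and to affected subjects whose SAE is thought manageable. None of it fixes when a hold must happen.

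A reader might also infer four stronger things that the protocol does not support:

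- **That escalation is automatic or obliges no group-level action.** The review is mandatory; only its outcome is open.
- **That the stop cannot operate because definitely related is not on the scale.** The term maps naturally to *Related*, and the rule turns on the judgement of the investigators and/or the Medical Director, not on a CRF category.
- **That the reference to Section 7.2 is wrong.** That section defines SAE and life-threatening. The reference is incomplete for causality only.
- **That a death would not stop the study.** A fatal event would ordinarily meet the definition of life-threatening in Section 7.2. Naming it is a clarification.

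Finally, 2 of 6 at grade 3 is one choice among several, and a weak detector: it holds in 34.5% of cases at a true rate of 20%. It can only be a floor under clinical review.

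**Conclusion.** The point holds in this form: escalation is reviewed but has no binding limit, and the mandatory stop is too narrow for a first trial of this product in healthy volunteers. Three plausible findings oblige no hold before the dose is doubled: a related SAE that is not life-threatening, a life-threatening SAE judged *Probably Related*, and several related grade 3 reactions at one dose. This is a safety rule that the protocol itself states, in its own section, so it is not detail left to an SAP.

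The conclusion rests on the text alone. How often the present review would hold cannot be derived from the document. The percentages above describe the example hold rule under assumed rates, independent subjects and all six reaching each step; they do not measure the defect. The change should be made before the first active dose.

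**What to change.** Amend Section 3.6 before Day 8:

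1. **Stop** the study for any fatal or life-threatening SAE judged *Probably Related* or *Related* (Section 7.1.1).
2. **Hold** dosing and escalation for any other SAE at least possibly related, and when a sponsor-set number of subjects (for example 2 of 6) have CTC grade 3 or higher events at least possibly related at the same active dose level. Resume only after documented review by the investigator and the Medical Director, with IRB notification. Section 10.3 does not compel an amendment in order to resume under a rule already written into the protocol.
3. **For both rules**, state that a reasonable temporal relationship without a clear alternative cause is enough, and that a known response pattern is not required.
4. **Cite Section 7.1.1** for causality in addition to Section 7.2.

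Below these thresholds the existing two-party review stays as it is. The exact count is for the sponsor to choose.

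The cost is a short rewrite of one section, with no new visit, measurement or committee. The downside is an occasional unnecessary hold, at the rates shown for 2 of 6, and a delay beyond the ±1 day visit window when one occurs.

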## Indication

For the treatment of Gaucher Disease

## Blinding

Not applicable

## Controls

Not applicable

## Randomization

No randomization

## Dose Rationale

In order to enhance the healthy volunteers’ safety, all 6 subjects will undergo a staggered dose escalation starting with vehicle only, followed by low dose of 15 units/kg, continued with 30 units/kg (moderate dose) and finally with the high dose of 60 units/kg. The last 2 doses are the ones planned for phase III study. The two higher doses have been used before with different enzymatic preparations and have been shown to be safe and effective in patients with Gaucher disease.

.

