## Rationale

Human glucocerebrosidase has been used successfully for the clinical treatment of Gaucher disease for several years from both natural and recombinant sources (CHO production platform). This is the first trial to utilize a recombinant active form of lysosomal enzyme, glucocerebrosidase, (human prGCD) which is expressed and purified in a bioreactor system from transformed carrot plant root cell line.

Since the glycosylation pattern of recombinant human glucocerebrosidase must possess high mannose structures to increase uptake in target cells, the expression of human glucocerebrosidase in plant cells could be of great value. As mentioned above several approaches are utilized to control and tailor protein glycosylation in plants (Dwek RA *et al*. 2002). Protalix’s approach attempts to localize the expression to a specific compartment in the cell. For example, retaining the protein in the endoplasmic reticulum (ER) prevents plant specific modification from being carried out in the Golgi (Neuhaus JM and Rogers JC 1998; Vitale A and Galili G 2001). This approach has been adopted in developing active human prGCD.

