## Summary of non clinical and clinical studies

Two GLP toxicology studies where performed and completed with the current human prGCD recombinant protein, derived from plant tissue culture bioreactor system. The first was a study in rodents, performed at Harlan Biotech Israel, In this study a single dose of: Vehicle; 1X; 5X; 10X of the clinical dose (60units/kg) were given to 24 mice. A 14-day observation period included clinical signs, body weight, detailed necropsy and gross pathological examination. In this study no obvious treatment related adverse reactions, no gross pathological findings, and no mortality were observed.

The second study was a 28 days repeat dose in non-human primates (Marmosets) preformed at Huntingdon Life Sciences Laboratory UK. Twenty-four (24) animals (4/sex/group/dose) were intravenously infused daily with 1X or 5X of the clinical dose (60units/kg) adjusted to animal body surface area The 1X clinical dose, 60U/kg, is equivalent to 1.8 mg/kg in humans which corresponds to 66 mg/m2 (using the standard human surface area conversion factor of 37). The dose of 66mg/m2 corresponds to 11 mg/kg in marmosets (using the conversion factor of 6 for marmoset monkeys). Therefore, 5 times the clinical dose is 55mg/kg in Marmoset monkeys.

In-life data were collected and analyzed. Preliminary results indicated no obvious treatment related adverse reactions, no gross pathological findings, and no mortality. Ophthalmoscopy and electrocardiography indicated no findings related to the treatment. In addition, all blood and urine tests were found to be within normal ranges for Marmosets. More detailed description of the above toxicology study can be found in the pre-clinical section in the Investigator’s Brochure.

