# STUDY DESIGN

The proposed investigation will be a phase I, single-center, non-randomized, open label, safety study of three single escalating doses of human prGCD administered as an intravenous infusion (IV) to six healthy volunteers. Subjects meeting the entry criteria will be eligible to receive study drug. Urine will be collected 24 hours prior to screening to assess renal function. Seven visits are scheduled for this study: pre-screening (Day -1), Screening (Day 0), baseline (Day 1), Visit 1 (Day 8), Visit 2 (Day 15), Visit 3 (Day 22) and follow-up visit (Day 29). The study procedures for each visit are presented in the study flow chart (Appendix 1). The duration of study is 29 days.

Subjects will be monitored over 24 hours from the commencement of the infusion of each dose at the Hadassah medical center, Phase I unit. The treatment will consist of a single dose infused for 1.5 hours (1.5mL/min). The infusion rate may be adjusted according to subject symptoms and signs: slower rate (1mL/min) upon adverse effect or faster (2mL/min.) upon lack of any symptom and signs. The vital signs for each subject will be monitored during infusion. ECG will be done at baseline and at 8 hours following the infusion. Subjects will remain at the clinic for 8 hours post-infusion and will be discharged if no AEs are observed. Subjects will return to the clinic 24h post initiation of infusion for additional safety assessment. Vital signs will be recorded during the infusion and PK sampling every 30 minutes (up to 3.5 hrs), and afterward at 8 and 24hrs post infusion.

Each subject will receive a single IV dose of vehicle at the baseline visit (Day 1). Blood samples for PK will be collected prior to dosing (0) and at 5, 45, 80 and 90 minutes during the infusion and 100, 115, 130, 150, 180, 210 minutes and 24 hours from initiation of infusion. On Day 8, subjects will receive a single 15 units/kg of study drug and will have the same blood samples taken as per Day 1. On Day 15, subjects will receive a single 30 units/kg of study drug and have the blood samples taken as per Day 1. On Day 22, subjects will be administered a single dose of study drug of 60 units/kg, and have the same procedures performed as Day 1.

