## Exclusion Criteria

Subjects will be excluded from the study if they:

1. Have clinical evidence of any active significant disease that could potentially compromise the ability of the investigator to evaluate or interpret the effects of the study treatment on safety assessment and thus increase the risk to the subject to unacceptable levels.
2. Are pregnant or nursing.
3. Presence of any acute or chronic diseases
4. Have a history of any allergies
5. Have been exposed to long-term steroid treatment
6. Had a major operation in last 6 months
7. Have ever been exposed to any previous recombinant protein therapy
8. Have received immuno-suppressive treatment
9. Have a positive HIV, HBsAg and HCV laboratory result
10. Use any medication in cases of chronic drug administration other than vitamins or oral contraceptive (for female).
11. Have participated in another clinical trial during the previous 3 months
12. Have history of alcohol or drug abuse
13. Are considered by the Investigator to be unsuitable candidate for this study

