## Screening Visit (Day 0), Screening Visit can be done 21 day before planned visit.

1. Investigator will review all inclusion and exclusion criteria and determine subject's eligibility
2. Informed consent is signed
3. Demographics (date of birth, gender, ethnic origin)
4. Medical history (including concomitant medication use and medical conditions)
5. Complete physical examination including vital signs (blood pressure and heart rate), body weight (kg) and height (cm)
6. Chest X-ray (if not obtained within the past 6 months prior to study start), if an Chest X-ray was done within the past 6 month the film must be available for reading by the PI
7. Electrocardiogram (ECG)
8. Withdrawal of 22 mL venous blood for laboratory tests, which include,:
   1. Serum chemistries including electrolytes (K, Na, Cl, HCO3, Ca, and P), liver function tests (AST, ALT, LDH, AlkP, GGT, and Bilirubin), Renal function tests (BUN, and Creatinine,) CPK, Serum proteins(Albumin,Globulin), Cholesterol, and Uric Acid
   2. Complete blood cell count including white blood cells differential count (CBC), and coagulation profile (PT, PTT)

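### No interval is set between subjects at the first prGCD dose, so all six volunteers may receive 15 units/kg before any 24 h data on the enzyme exist

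*Protocol*

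**What the plan says.** Each of the six subjects receives vehicle on Day 1 and then 15, 30 and 60 units/kg on Days 8, 15 and 22 (Section 3, Section 5.4, Appendix 1). Each visit has a window of ±1 day.

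- **Spacing.** Section 3.5 states that "all 6 subjects will undergo a staggered dose escalation starting with vehicle only, followed by low dose of 15 units/kg". The sentence goes on through the two higher doses, so the stagger is over dose levels. Section 3 says: "On Day 8, subjects will receive a single 15 units/kg of study drug". Neither these sections nor Appendix 1 names a lead subject, a minimum gap between subjects or a limit on subjects per day.
- **First complete post-dose check.** Section 3: "Subjects will return to the clinic 24h post initiation of infusion for additional safety assessment". The 24 h visit includes chemistry, blood count, coagulation and C3 (Section 5.4).
- **Review gate.** Section 3: "The Principle Investigator will review all test results and AE report 24h prior to escalation to the next dose level". The investigator and the sponsor's medical director then decide on the increase.
- **Novelty.** Section 1.1: "This is the first trial to utilize a recombinant active form of lysosomal enzyme, glucocerebrosidase, (human prGCD". The material comes from a carrot cell line.
- **Stopping.** Section 3.6 stops the study for a serious event judged both life-threatening and definitely due to the drug. Section 8 allows withdrawal of a subject, or discontinuation by the sponsor, on judgment.

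**The concern.** The first 15 units/kg infusion is the first human exposure to this product, and it is the one step at which the review gate holds no information about the enzyme. At 30 and 60 units/kg, the review can use data from the level below. At 15 units/kg it can use only vehicle data.

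If all six are infused on the same day, a reaction that appears after the infusions have begun, or only in the 24 h laboratory results, comes too late to spare anyone. The stopping rule does not fill this gap: it acts after an event, and its threshold excludes a severe reaction that is not life-threatening. The subjects are healthy volunteers, and Section 9.2 lists infusion-related toxicity first among the safety parameters. PK and antibody samples are analyzed only at the end of the study, so the 24 h visit is the earliest complete post-dose assessment available while the trial runs.

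**Working it through.** The plan gives no reaction rate and no sample size calculation, so there is no figure of its own to reproduce. The check has three parts.

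**1. What the schedule permits.** Before the first active dose, 0 of 6 subjects have post-prGCD data. With no interval between subjects, up to 6 of 6 may be exposed before the first 24 h visit. With one lead subject, 1 of 6 is exposed by then.

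**2. What a lead subject would gain.** Let p be the chance that a subject has, within 24 h, a reaction that would stop further dosing. The documents do not give p, so it is assumed.

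- Expected number exposed with a lead subject, the other five being dosed only if the lead has no such reaction: 1 × p + 6 × (1 − p) = 6 − 5p.
- Without a hold, up to 6 are exposed, so the largest gain is 6 − (6 − 5p) = 5p.
- Suppose one infusion happens to start first, and a share f of such reactions shows before the others start. The gain from the 24 h hold is then 5p(1 − f).

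| p (assumed) | Exposed with lead subject | Gain, f = 0 | Gain, f = 0.5 | Gain, f = 1 |
|---|---|---|---|---|
| 1% | 5.95 | 0.05 | 0.025 | 0 |
| 10% | 5.5 | 0.5 | 0.25 | 0 |
| 30% | 4.5 | 1.5 | 0.75 | 0 |

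The chance of two or more reactors moves the same way. With all six dosed together it is 1 − (1 − p)^6 − 6p(1 − p)^5. With a lead subject it is (1 − p) × [1 − (1 − p)^5 − 5p(1 − p)^4]. At p = 10% these give 0.114 and 0.073; at p = 30%, 0.580 and 0.330.

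Nominal animal margins at the starting dose (Section 1.2) are 10 × 60 / 15 = 40 for the single mouse dose and 5 × 60 / 15 = 20 for the daily marmoset dose, which was adjusted for body surface area.

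**3. Whether a hold fits the calendar.** Day 8 ± 1 gives Days 7 to 9.

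- Lead subject on Day 7, 24 h visit on Day 8, other five on Day 9 (or on Day 8 if the results are back). The last 24 h visit is then no later than Day 10.
- The review before a Day 15 dose is due on Day 14, which leaves 14 − 10 = 4 days, or 3 days if the next dose is given on Day 14.
- With vehicle on Day 1, the gap to the first active dose is 7 − 1 = 6 days for the lead and 9 − 1 = 8 days for subjects dosed on Day 9. The gap to Day 15 is 15 − 7 = 8 and 15 − 9 = 6 days. All lie within the 7 ± 2 = 5 to 9 days that the windows already allow between consecutive doses.
- Alternatively, the lead subject's whole calendar starts two days earlier. The lead is dosed on calendar day 8 and seen on day 9. The others are dosed on day 10, which is their own Day 8, and seen on day 11. The lead's next level is due on day 15 and the review on day 14, which leaves 3 days.

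**The case against.** The strongest reply is that this is a design preference in a plan that already protects its subjects well.

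- **Experience with the enzyme class.** The Introduction reports 14 years of replacement therapy in over 3000 patients. Section 3.5 notes that 30 and 60 units/kg were given before with other preparations. The starting dose is half the lower of these.
- **Animal data.** The margins are 40 and 20. For the marmosets, "Preliminary results indicated no obvious treatment related adverse reactions, no gross pathological findings, and no mortality".
- **Selection.** Section 4.2 excludes volunteers who "Have a history of any allergies", and anyone with earlier recombinant protein therapy.
- **Monitoring.** There is a vehicle run-in, vital signs are taken every 30 minutes, the infusion can be slowed, and subjects stay 8 h with an ECG and are discharged only if free of adverse events.
- **Stopping.** The rule in Section 3.6 is narrow but mandatory.
- **Calendar.** "Screening Visit can be done 21 day before planned visit", and nothing obliges the six to start together, so a natural gap may arise.
- **Size of the gain.** Acute reactions, where a hold should help most, are also those most likely to be seen during a monitored infusion. If infusions start one after another, f may be high and the gain small. A same-day gap between starts could capture part of the benefit.

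All of this stands, and it limits the priority. It does not remove the point. These measures make a reaction less likely or easier to manage, but none obliges the other five to wait. The experience in patients is with other products, and the marmoset results are described as preliminary. A natural gap is possible but not required, and a same-day gap would not give the 24 h laboratory results.

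A reader might also infer that the escalation review is faulty because it does not say that it covers the whole cohort. The documents do not support this. It calls for all test results and most naturally means one review of all subjects, so no rewording is proposed.

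**Conclusion.** The point holds as a cheap improvement of modest priority. The plan permits, but does not require, all six first exposures to prGCD before any subject's 24 h data exist, and the review before that step can contain vehicle data only.

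The expected reduction in exposed subjects is at most 5p: negligible at 1% and 1.5 of 6 at 30%. It approaches zero if reactions show before the others are infused. Both p and f are assumptions. The value lies mainly in reactions that affect many recipients and are not visible before the other infusions start.

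Two stronger readings are tempting and unsupported. One is that the protocol orders simultaneous dosing, or contradicts itself by using the word staggered. It leaves the timing between subjects open, and the word is explained by the dose sequence in the same sentence. The other is that volunteers are left unprotected. The safeguards above are real, and no figure in the documents shows a high reaction risk.

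**What to change.** In Sections 3 and 3.5 and Appendix 1, add for 15 units/kg only: one lead subject is dosed first, and the other five are dosed only after the investigator has reviewed that subject's 24 h visit, including the 24 h laboratory results then available.

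Two timetables work:

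- **Within the ±1 day window:** lead on Day 7, others on Day 9, or on Day 8 if the results are back. This costs one extra dosing day. Subjects dosed on Day 9 have no room left to slip.
- **Offset calendar:** the lead subject starts two days before the others, which keeps everyone's nominal days and leaves the window free. This costs four extra dosing days, one per infusion visit.

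Neither needs extra subjects, visits or tests. Both need coordinated starts, which the 21-day screening allowance helps, and a delay in the lead subject can hold up the others. No hold is needed at 30 or 60 units/kg.
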